**List of acronyms and abbreviations**

DHB District Health Board

HRQoL Health related quality of life

DSSI Duke Social Support Index

SF36 Short Form 36

EADL Extended Activities of Daily Living

BOP Bay of Plenty

COPD Chronic Obstructive Pulmonary Disease

AMTS Abbreviated Mental Test Score

# Background

**Telecare** is a new development in New Zealand. It combines **self-monitoring -** whereby people with long term conditions monitor their symptoms to track progress, modify behaviours, or medications accordingly or assess when to seek help from health professionals (Singh, 2005) - with **tele-medicine** which is described as the use of telecommunications technology for medical diagnostics, monitoring, and therapeutic purposes when distance and/or time (or access) separates the participants AHRQ (2006).

**ASSET** is:

1. the first stage of developing a programme of randomised controlled trials to assess the effectiveness of telecare in New Zealand; and
2. a systematic service development that will have multiple outputs of direct value in its own right.

It will be conducted in four study sites (Auckland, Counties Manukau, Tairawhiti and Canterbury). Each study site involves a distinct population group and service model though share some outcomes and telecare product.

**Terminology**

We use the word **‘patient’** to designate the person who is the subject o f care, the person with the long term condition. We use the term **‘family’ or ‘family / whanau’** to designate the others living in the household with the patient, or who provide substantial health care to the patient on the basis of their relationships to the patient, not in a professional relationship. We use the word **‘participant’** to refer to any or all of the patient, family / whanau, and all the health care professionals involved in the patient’s usual care or telecare. We use **‘clinician’ or ‘health professional’** interchangeably to refer to doctors, nurses, pharmacists and other relevant professionals.

It should be noted that the quantitative components of ASSET will develop **pilot data in the New Zealand context to inform sample size calculations** with respect to effect size and frequency of events. **It is not powered to definitively confirm effectiveness for most outcomes** (see power calculations). These requirements will be addressed in subsequent studies.

It should also be noted that ASSET will in effect form a **process map of ‘usual care’**, which is necessary to develop agreement with health care providers on developing and definitively measuring the effects of telecare.

# Research hypotheses

These hypotheses underlie the current ASSET trial *and* the intended follow up trials.

That, compared to ‘usual care’, for people with specific long term conditions, telecare will:

1. Increase the health related quality of life (HRQoL) and satisfaction with health services for patients and family / whänau;
2. Decrease hospital attendance and admissions;
3. Improve the HRQoL of the primary informal caregiver;
4. Provide an economically more efficient means for the person, family / whänau, providers and funding agency to manage a person’s chronic condition;
5. Be feasible and acceptable to patients and health care professionals
6. Be an enabler for the integration of health services;

# Study Design

ASSET will be conducted as:

- **Three separate randomised controlled trials** in Auckland, Counties Manukau and Canterbury (there will be no control group in Tairawhiti)
- Within each of the active intervention arms, including Tairawhiti, there will be an **action research process to optimise the telecare system intervention.**
- Within each control arm there will be a **process of mapping real usual care.**

Each region will stand alone as a discrete trial though with some shared outcomes. Standard criteria and measures will apply across all trials.

The telecare equipment will be available to all four health services for 12 months, with equipment loaned to any one patient for up to three months.

Participants will be assessed at baseline with follow up at three (immediately post intervention) and six months (three months post intervention).

# The comparison groups

The interventions to be evaluated are:

1. the specialist heart failure service with telecare compared with the existing heart failure specialist services in Auckland (for heart failure);
2. the specialist respiratory service with telecare compared with existing respiratory services in Counties Manukau (for COPD);
3. the Ngati Porou Hauora chronic care programme with telecare compared with the existing chronic care management programme in Tairawhiti (for multiple long term conditions); and
4. the community specialist respiratory medicine service with telecare compared with existing respiratory services in Canterbury (for COPD).

# Ethics

We will apply to the Ministry of Health Northern Ethics Committee. No patients will be enrolled before ethics approval is obtained.

A researcher will provide an approved participant information sheet to all people who are potentially eligible to participate. In Auckland, Counties Manukau and Canterbury, those who provide written consent will have baseline data collected and will then be randomly allocated to intervention or control arms. From those who do not consent to participate we will seek to obtain basic demographic information. In Tairawhiti all participants will be included in the active development and observation programme.

# Eligibility

**Inclusion criteria:**

1. *All areas*
   1. age 16+
   2. living permanently at home
   3. expected to be available for 3 months
   4. expected to survive study period
   5. able to communicate in English (or someone in household able to translate)
   6. able to physically manage the equipment (or someone available to assist)
2. A*uckland* – Permanently resides in the Auckland DHB region, current or recent in-patient to Auckland City Hospital with heart failure as the primary reason for admission
3. *Counties Manukau* – Permanently resides in the Counties Manukau DHB region, enrolled with ProCare PHO, current or recent in-patient at Middlemore Hospital with COPD as the primary reason for admission
4. *Tairawhiti* – Permanently resides in the Tolaga Bay area, enrolled with Ngati Porou Hauora PHO, and is on the PHO chronic condition management programme
5. *Canterbury* – Permanently resides in the Canterbury DHB region, enrolled with practices working with the community specialist respiratory service, with COPD being treated with Long Term Oxygen Therapy (LTOT) at home

**Exclusion criteria:**

1. Significant cognitive impairment (<8/10 Abbreviated Mental Test Score - AMTS)
2. Serious current physical or mental illness
3. Previously used telecare

# Recruitment

**Numbers potentially available**

*Auckland* – about 5000 known patients with CHF, about 500 admissions, about 300 admissions with ‘new’ CHF per year

*Counties Manukau* - About 600 ‘new’ COPD patients are admitted to hospital each year

*Canterbury* - about 500 ‘new’ COPD patients are admitted to hospital each year; 250 on LTOT at any one time

*Tairawhiti* – to a maximum of 50 participants at any one time

**Recruitment strategies:**

*Auckland* – identified by CNS on admission with CHF, screened for eligibility and consent to pass name to researcher, who will conduct formal consent process.

Counties Manukau - identified by CNS on admission with COPD, screened for eligibility and consent to pass name to researcher, who will conduct formal consent process.

Tairawhiti – identified by chronic care nurse, from current register of community patients, she will screen for eligibility and conduct formal consent process.

Canterbury - identified by CNS on admission with COPD, screened for eligibility and consent to pass name to researcher, who will conduct formal consent process.

# Baseline and repeated assessments

All study participants, in intervention and control groups, will have the same data collected relating to quality of life and resource use at baseline, 3 months and 6 months.

Those in the intervention arm will be asked additional questions relating to the technology, at 3 months and 6 months.

For baseline data collection see **Appendix 1**.

# Randomisation and study group assignment

Immediately after baseline data collection, participants in Auckland and Counties Manukau will be randomised to intervention or control arms. The researcher will phone an Interactive Voice Response (IVR) system via an 0800 number, provide basic patient identification data and be assigned a study group for that patient.**

*Eligible  consent  baseline data collection  individual randomly assigned to intervention or control*

In Christchurch, a pre-assigned cluster randomisation will assign participating general practice surgeries – and the patients attending them – to intervention or control arms of the study.

*Eligible  consent  baseline data collection  cluster randomised to intervention or control, based on randomly assigned group of patient’s general practice*

In Tairawhiti, patients will not be assigned to separate groups.

*Eligible  consent  baseline data collection  followed in telecare programme*

Note: initially we intended to randomise with stratification by age / gender / distance from hospital / ethnicity. We have decided against this as i) we are collecting pilot data and will find if we obtain an adequate stratification by including all who are eligible and consent ii) there are technical and efficiency reasons not to stratify. From this pilot data we will be better informed as to whether stratification will be necessary in a follow up trial.

# Qualitative interviews

While the core research in this project is aimed at establishing the purpose, design and evaluation of telemonitoring as a clinical intervention, there are other key components of telehealth that lend themselves to measurement. They include

- **Business implications of telemonitoring**
  - How ‘usual care’ is performed as a business process in both primary and secondary care (processes as they are currently done/used)
  - What the implications of telemonitoring are on ‘usual care,’ e.g. what happens when care is shared between specialist, primary care doctor and chronic care nurse, and how this contributes to the concepts of ‘integrated care’ or ‘shared care’ (process changes as a consequence of telemonitoring)
- **Chronic condition management implications**
  - What the impact is on chronic condition self management, and how the potential for self care can be supported using telemonitoring (self care as it is currently done and consequent changes resulting from telemonitoring)
- **Criteria for including people in a telemonitoring mode of** **care.** It is not clear in the literature how people are selected for telemonitoring. Most of the literature surveyed provides evidence THAT there are benefits associated with telemonitoring, but no clear guidance is given for deciding how to select users.
- **Criteria for exiting people from a telemonitoring mode of care.** It is not clear how a decision is made that a person either no longer benefits from telemonitoring or would benefit more from exiting such a programme.
- **Cost analyses of using telemonitoring.** The literature does not provide complete, sufficient or comprehensive information on cost analyses.

Potential participants for this set of research projects include the ‘actors’ listed below as described by Mantzana et al 1 (in no particular order). These participants will be identified using the Balanced Score Card and the person centric continuity of care model for people with chronic conditions developed by Warren et al 2.

- **In primary and secondary care services,** clinicians (doctors, nurses and allied health care personnel associated with people receiving care for chronic conditions), managers and administrative staff will be approached to participate in this research to
  - **Before recruiting patients for telemonitoring**
    - Describe current care processes and identify clinical guidelines and protocols in use as benchmark of best practice for people with chronic conditions relating to this project 3 4
    - Reflect on and document current ‘usual care’ and associated processes, workflow and routines e.g. emergency care admission process of patients already receiving specialist care 5.
  - **After one year of patients using telemonitoring,** in a semistructured interview, they will be asked the questions outlined in Appendix 3.
- **In the community,**  people with chronic conditions (as identified by their clinicians for inclusion in the telemonitoring project), their family members (and Whanau) and their extended social supports (friends, co-workers and others deemed appropriate for participating in the research) will be approached as follows.
  - **‘Patients’ will be invited to participate regarding their perceptions of self management of their chronic condition as follows**
    - The ‘patients’ will be interviewed regarding their self-care capacity, using the questionnaires from the Flinders model 6. The twelve questions from the Partners in Health Scale (see Appendix 3) will be used to establish the degree to which patients are managing their own condition.
    - Further questions will be asked in terms of patient perceptions of their clinical outcome from the telemonitoring intervention and compared with that of their clinicians.
    - They will be asked these questions at the beginning and end of their use of telemonitoring to establish if the intervention made any change to their sense of self management.
  - **‘Patients’ and their family members who share care with them will be asked about their propensity to use technology as follows.**
    - Based on the Technology Adoption Model by Davis as used by Rahimapour et al 7 we will ask questions about perceptions of usefulness of the telemonitoring kit (see Figure 2 for the questions). These questions will be used as a guide to frame reflection about how the technology was seen to be useful for self management. Other questions are added as indicated in Appendix 3.
    - This semistructured interview will be done in the third month in which a ‘patient’ uses the telemonitoring kit.

**The ASSET project team will be invited to reflect** on the following questions

- How does the telehealth intervention change equity, equality, empowerment, trust among clinicians, monitoring of patients in their home, effect of surveillance, therapeutic or dehumanizing effect, different meanings of information? 5
- To what extent does the information system meet the project’s requirements as well as objectives?3
- What can be generalised/transferred to another study/setting?5

In addition, the team members will be asked to reflect on the project using the REFLECT mnemonic as outlined by Day, Orr, Sankaran & Norris 8 as follows:

“...**R**eview thoughts, feelings, behaviour linked to planned and unplanned action; we look for **E**xceptions when everything appears to be going well; we consider the **F**uture impact such as identifying the next step in our activities; we **L**earn as we consider opportunities for building models and enhancing our understanding; we seek **E**xplanations when things are in apparent disagreement; and we **C**hallenge assumptions and consider what **T**roubles or puzzles us about our observations.” (p. 3).

This form of reflection will be conducted at the end of the first year and will be used to float ideas, thoughts and observations about the intervention that could be useful for future research. Using a complexity theory approach 9, this form of reflection can raise emerging concepts, patterns and practices in ways that can be further researched.

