# Describing usual care

The researchers will use an observation and interviews, as above, to decribe and document ‘usual care’ at each site.

As part of this process we will ask each CNS to keep a diary of costs and resource use for 1 month, and each patient/whanau participants to keep a diary of costs and resource use for 2 weeks.

In addition, each patient in the usual care group will be asked to complete the same interview and questionnaire schedule as the Intervention group, less the technology-specific components.

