# Analysis

Primary quantitative analysis will be by Intention to Treat (i.e. as planned) and modified Intention to Treat (i.e. as delivered). Exploratory analysis will assess the influence and associations of explanatory and potentially confounding variables. The findings will help determine whether randomization for subsequent trials needs to be simple or stratified.

Subgroup analysis will be employed, where possible with the number of patients in each group, to detect clinically important differences between subgroups that may be defined by age, gender, ethnicity, rural-urban dwelling and severity of initial health assessments.

There will be no imputation of missing data. All analyses will be conducted in Stata. Continuous variables will be analysed using mixed effects models that included site as a fixed effect, patient as a random effect and adjusted for age and gender. The main outcome for the psychometric scales will be assessed from the interaction between intervention group and time. Negative binomial regressions will be used to model count data including numbers of hospital attendance, length of stay and costs in analyses were adjusted for patient age, gender, ethnicity, and site as a factor variable. Exposure, for hospital use, will be measured by days alive and not in hospital. Exposure, for total days in hospital, will be measured by days alive. Results will be considered statistically significant when p ≤ 0.05.

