# Summary of data collection at each time point

|  | **At beginning of each patient telemonitoring** | **At end of each patient telemonitoring** | **At end of project** |
| --- | --- | --- | --- |
| **patients** | **Baseline data collection**  **SF36**  **Stanford self-efficacy scale**  **Semistructured interview based on PIH**  **Disease specific questionnaire**  **1. St George Respiratory Questionnaire**  **2. COPD Helplessness Index**  **3. Minnesota Heart Failure questionnaire (?)** | **SF36**  **Stanford self-efficacy scale**  **Semistructured interview based on PIH**  **Disease specific questionnaire**  **1. St George Respiratory Questionnaire**  **2. COPD Helplessness Index**  **3. Minnesota Heart Failure questionnaire (?)** |  |
| **Patient whanau / support people** | **Semistructured interview based on PIH** | **Semistructured interview based on PIH** |  |
| **clinicians** |  |  |  |
| **Clinicians, administrators** |  |  |  |
| **Research team** |  |  | **Interview using REFLECT model** |

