# Appendix 3. Interview schedules

**Interviews with patients, about self-care, at the beginning and end of their telemonitoring**

Semi-structured interviews with patients, based on 12 areas of the Flinders Partners in Health Scale.6

1. Knowledge of condition
2. Knowledge of treatment
3. Ability to take medication
4. Ability to share in decisions
5. Ability to arrange and attend appointments
6. Understanding of monitoring and recording
7. Ability to monitor and record
8. Understanding of symptom management
9. Ability to manage symptoms
10. Ability to manage the physical impact
11. Ability to manage the social and emotional impact
12. Progress towards a healthy lifestyle.

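### Whether telecare changed self-management should be judged against the usual-care patients who already give the same interview, not from telecare users' start and end answers alone

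*Protocol*

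**What the plan says.** Five places in the protocol bear on this.

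- *Qualitative interviews* bases patients' self-care assessment on the twelve Partners in Health questions and has them asked "at the beginning and end of their use of telemonitoring to establish if the intervention made any change to their sense of self management". It mentions no usual-care comparison.
- *Appendix 3* describes the instrument as "Semi-structured interviews with patients, based on 12 areas of the Flinders Partners in Health Scale" and uses the same start-and-end timing. *Qualitative analysis* assigns interview material mainly to thematic analysis.
- *Describing usual care* says "each patient in the usual care group will be asked to complete the same interview and questionnaire schedule as the Intervention group", leaving out only the parts about the technology. The control data are therefore planned.
- *Summary of data collection at each time point* puts the Partners in Health interview in two columns, for the beginning and the end of telemonitoring (the second is headed "At end of each patient telemonitoring"). SF36, the self-efficacy scale and the disease-specific questionnaires stand in the same columns.
- *Analysis* says "The main outcome for the psychometric scales will be assessed from the interaction between intervention group and time". It does not list which scales this covers, and Partners in Health is not among the scales named in *Outcome Measures*.

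**The concern.** Asking whether the intervention made a change is a question about cause. A start-to-end difference in telecare users answers it only if nothing else would have moved their answers over the same months, and this protocol gives reasons to doubt that.

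Auckland takes a "current or recent in-patient to Auckland City Hospital with heart failure as the primary reason for admission", and Counties Manukau has the equivalent criterion for COPD. *Recruitment strategies* has Canterbury patients identified on admission too, although Canterbury eligibility is defined by long-term oxygen at home. Many baseline interviews will thus fall at or near an acute episode. Recovery, teaching given at discharge and the experience of repeating the interview could each change how patients describe their self-management, in either arm.

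The protocol presents the study as a source of information for later trials. Ordinary recovery read as a benefit of telecare would mislead their planning, although the comparison needed to prevent this is already being collected.

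**Working it through.** **1. Is there a figure to reproduce?** No. The protocol gives no sample size, error rate, score or test for this interview. The arithmetic below shows how a before-after contrast behaves; it does not check a stated figure.

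**2. Inputs from the protocol.**
- Telecare patients per randomised site: 48 (Appendix 8; 12 months × 4 per month).
- Drop-out: about 20% (*Statistical Issues*), so 48 × 0.8 = 38.4, or about 38 with both interviews.
- Significance level: 0.05 (*Analysis*), taken here as two-sided.

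**3. Assumptions not in the protocol.**
- The twelve areas are scored and a paired t-test is applied to telecare users only.
- Telecare has no effect, and both arms shift by the same drift d, in units of the between-patient SD, from 0 to 0.5.
- The start-end correlation r is 0.5 or 0.7.

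**4. Formula.** The SD of the change is √(2(1 − r)), which is 1 at r = 0.5 and √0.6 = 0.775 at r = 0.7. The noncentrality parameter is d × √n ÷ √(2(1 − r)). For n = 48 and r = 0.5 it is 6.93 × d: 0.69, 1.39, 2.08 and 3.46 at d = 0.1, 0.2, 0.3 and 0.5. The chance of declaring a change is the probability that a noncentral t on n − 1 degrees of freedom falls outside the two-sided 5% limits.

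**5. Chance of declaring a change when telecare does nothing.**

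| n | r | d = 0 | 0.1 | 0.2 | 0.3 | 0.5 |
|---|---|---|---|---|---|---|
| 48 | 0.5 | 5% | 10% | 27% | 53% | 92% |
| 38 | 0.5 | 5% | 9% | 22% | 44% | 85% |
| 48 | 0.7 | 5% | 14% | 42% | 75% | 99% |
| 38 | 0.7 | 5% | 12% | 34% | 64% | 97% |

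**6. The same situation compared between arms.** A two-sample t-test of change was simulated 20,000 times per setting (38 or 48 per arm, r = 0.5, drift 0, 0.2, 0.3 or 0.5 SD in both arms). It declared a difference in 4.8% to 5.1% of trials. Drift common to both arms cancels. The simulation assumes independent patients, so it does not represent Canterbury, where practices are randomised.

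**7. Is the end time point the same for both arms?** Usual-care patients have no end of telemonitoring, so their second interview needs a time counted from enrolment. For Canterbury the protocol gives two telecare periods. *Study Design* lends equipment to a patient for up to three months and calls the three-month visit immediately post-intervention; Appendix 8 plans six months per patient. Until these are reconciled, the end interview could fall at different times in the two arms.

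**The case against.** The strongest reply is that the quoted sentence says when the questions are asked and why, and sets no decision rule. The instrument is a semi-structured interview bound for thematic analysis, with no score, threshold or test. This stands. A reader might infer that the trial will declare a telecare effect 53% to 92% of the time in error. The protocol does not support that, because the paired t-test and the drift are both supplied here. At zero drift the error is the nominal 5%.

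A reader might also infer that the randomised comparison is discarded. It is not: the section is silent about controls, and giving them the same interview suggests that a comparison was in mind. The summary table does not show otherwise. Its telemonitoring column headings also cover SF36 and the self-efficacy scale, so they look like shorthand for baseline and follow-up.

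Third, the closest quantitative measure, the self-efficacy scale, is a primary scale, and psychometric scales are assessed by group and time. If Partners in Health counts as such a scale, a between-arm analysis already exists. This limits the reach of the point, but the protocol does not say that it counts, and the two sections would then need to be brought into line.

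Finally, the secondary outcome on adopting a self-management programme should not be equated with patients' sense of self-management.

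What survives is narrow: a causal purpose is stated, the only contrast named cannot serve it, and the comparator is at hand. That holds with or without a p-value. Leaving detail to an analysis plan does not answer it, since the purpose and the contrast are set out in the protocol itself.

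**Conclusion.** The point holds as one of inference. As worded, the Qualitative interviews section would establish an effect of telecare on self-management from telecare users' start and end answers, with no comparator named, and that contrast cannot tell telecare from recovery, discharge teaching or repeat interviewing.

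The size of the bias is unknown, because the protocol gives no drift or correlation. In the illustration it is negligible without drift and becomes serious from about 0.2 SD. The case for drift is clearest in Auckland and Counties Manukau, less clear in Canterbury, and not made by admission timing in Tairawhiti, which recruits from a community register.

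The consequence is limited to one secondary interview component. The primary scales and hospital-use outcomes are untouched.

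**What to change.** Add to *Qualitative interviews* wording to this effect:

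> At the three randomised sites, any effect of telecare on self-management will be judged by comparing the intervention and usual-care arms at the same time points after enrolment. Change within an arm, and all change in Tairawhiti, is descriptive only.

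Then settle three matters.

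- **If the twelve areas are scored:** use the group-by-time analysis in *Analysis*, allowing for practice clusters in Canterbury. The model described there has site and patient terms but none for practice.
- **If they stay unscored:** compare themes between the arms.
- **Timing:** reconcile the three-month and six-month telecare periods given for Canterbury, so that the end interview falls at the same time in both arms.

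The cost is small. Usual-care patients are already due to complete the interview, so no new data collection is needed. Scoring would add a scoring rule and a practice term in the model; leaving the areas unscored needs only the between-arm reading of themes.
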